## Section L. Monitoring and oversight

### 1. Who will be responsible for day-to-day supervision of the research?

[name] and [name] [name] will be responsible for day-to-day running of the research. [name] will supervise them and the study throughout this research.

Regular monitoring will be performed by the study team. Data will be evaluated for compliance with the protocol and accuracy in relation to source documents. The monitors will verify that the clinical study is conducted and data are generated, documented, and reported in compliance with the protocol, GCP and the applicable regulatory requirements.

### 2. Give information about frequency of meetings that will be held to discuss progress/problems. Who will be present at the meetings?

#### *Study management group*

The study management group will comprise of all named investigators and it will be responsible for the day-to-day running of the study and meet monthly to evaluate progress. Study coordinators and [name] will meet weekly every two weeks to evaluate progress. The frequency of the meetings may be adjusted depending on the progress.

#### *Study steering committee*

The committee will consist of clinicians with relevant clinical expertise and experience in clinical trials. They will not be members of the University of Oxford and not related to the investigators. According to NIHR's Research Governance guidelines, the SSC will examine the protocol and give advice on the conduct of the study and take on the roles of the DMEC with respect of monitoring safety if this is required. This is an open-label trial where the interventions are dietary and not known to cause harm and there are no early stopping rules that would require this. The SSC will receive and review information on the progress and accruing data of the trial and will provide advice on the conduct of the study to the investigators.

## Section M. Ethical and regulatory considerations

### Declaration of Helsinki

The Investigator will ensure that this research is conducted in accordance with the principles of the Declaration of Helsinki.

### Approvals

The application form/protocol, informed consent form, participant information sheet and any proposed advertising material will be submitted to the Medical Sciences IDREC for written approval.

The Investigator will submit and, where necessary, obtain approval from the above parties for all amendments to the original approved documents.

### Annual Progress Report

The CI shall submit an Annual Progress Report to the Medical Sciences IDREC within one month of the anniversary of approval.

## Section N. Insurance

The University has a specialist insurance policy in place which would operate in the event of any participant suffering harm as a result of their involvement in the research (Newline Underwriting Management Ltd, at Lloyd's of London).

## Section O. Dissemination and feedback of research outcomes

|                                                                                 |                                                                                                                                                                                                                                                                                                                                            |                             |
|---------------------------------------------------------------------------------|--------------------------------------------------------------------------------------------------------------------------------------------------------------------------------------------------------------------------------------------------------------------------------------------------------------------------------------------|-----------------------------|
| 1. Will you preregister this research?                                   | Yes                                                                                                                                                                                                                                                                                                     | No  |
| 2. If yes, please state the platform where it will be preregistered      | We will register the study at https://clinicaltrials.gov/ , once ethical approval is confirmed.                                                                                                                                                                                                  |                             |
| 3. How will you disseminate project outcomes at the end of the research? | The protocol and results will be published in open access journals and will be presented in conferences nationally and internationally. We will also compile a results summary for participants and lay members, to be disseminated to the study participants and other relevant partner organisations, stakeholder groups, and charities. |                             |

## Section S. Amendment history

List details of all protocol amendments here whenever a new version of the protocol is produced.

*This is not necessary prior to initial ethics submission.*

| Amendment No. | Protocol Version No. | Date issued | Author(s) of changes | Details of Changes made |
|---------------|----------------------|-------------|----------------------|-------------------------|
|               |                      |             |                      |                         |

| Documents Submitted for Review                    |                                            |                                           | New Version No. |
|---------------------------------------------------|--------------------------------------------|-------------------------------------------|-----------------|
| Updated CUREC form (required for most amendments) | YES
 | NO
            | N/A             |
| Revised Advertising Material                      | YES
            | NO
 |                 |
| Revised Information sheet(s)                      | YES
            | NO
 |                 |

| Documents Submitted for Review                                                 |                                            |                                           | New Version No.                                       |
|--------------------------------------------------------------------------------|--------------------------------------------|-------------------------------------------|-------------------------------------------------------|
| Revised Consent form(s)                                                        | YES
            | NO
 |                                                       |
| Other revised documents (please list)                                   | YES
 | NO
            | APPENDIX 16.
Qualitative
interview
questions |
| Email / Letter from Sponsor approving this amendment
(if applicable) | YES
            | NO
 | N/A                                                   |
| New documents (please list)                                             | YES
            | NO
 |                                                       |

## Main Changes Proposed in this Amendment

Please list the changes proposed with reasons for making the change in the table below. Refer to the examples provided at the top of the table and add further lines if required.  
There is no requirement to detail the exact changes made to each document, since these will be shown as tracked changes on the document.

| Proposed Change                                                                                                                                                                                | Reason for Request                                                                                                                                                                                                                                                                                                                                                                                                                                                                                                                                                                                                                                                                                                                                                                                                            |
|------------------------------------------------------------------------------------------------------------------------------------------------------------------------------------------------|-------------------------------------------------------------------------------------------------------------------------------------------------------------------------------------------------------------------------------------------------------------------------------------------------------------------------------------------------------------------------------------------------------------------------------------------------------------------------------------------------------------------------------------------------------------------------------------------------------------------------------------------------------------------------------------------------------------------------------------------------------------------------------------------------------------------------------|
| Example: Extension of REC approval from current end date of 31 Dec 2017 to 31 Dec 2018                                                                                                  | Example: Recruitment has been slow                                                                                                                                                                                                                                                                                                                                                                                                                                                                                                                                                                                                                                                                                                                                                                                     |
| Example: Addition of a new sub-study                                                                                                                                                    | Example: Findings to date have been interesting and we would like to include further investigations to corroborate our data                                                                                                                                                                                                                                                                                                                                                                                                                                                                                                                                                                                                                                                                                            |
| 1. Replace “registered dietitian” with “supervised by a dietitian”                                                                                                                             | 
There are three reasons for this change: first, we are short of registered dietitians to deliver support calls, so our registered dietitians will arrange training for new researchers. These researchers will initially deliver the calls under the supervision of our registered dietitians to ensure quality. They will conduct the calls independently but will seek advice from registered dietitians as needed.
 
Second, our support calls do not involve extensive nutritional advice, and our dietitians have collected and prepared common questions with correct answers, so this change will not affect the integrity of the intervention.
 
Third, this change is safe for our participants because patients with special dietary requirements or bowel issues were not included in this study.
 |
| 2. We have revised “APPENDIX 16. Qualitative interview questions” to use more conversational language and added further questions about patients' experiences and attitudes towards the meals. | This change helps researchers follow the process more easily, facilitates our conversations with participants, and increases our understanding of how patients feel about the entire study.                                                                                                                                                                                                                                                                                                                                                                                                                                                                                                                                                                                                                                   |

## Version history

| Version: | Version Date:    | Changes:                                 |
|----------|------------------|------------------------------------------|
| 4.0      | 12 December      | Final version                            |
| 3.0      | 28 November 2024 | Add "5. SECONDARY ANALYSIS"              |
| 2.0      | 30 October 2024  | Update the CONSORT flow diagram          |
| 1.0      | 9 September 2024 | Addition of information on data analysis |

## 1. INTRODUCTION

### 1.1. PREFACE

The Chief Investigator will run the statistical analysis. The investigators and the Trial Statistician have reviewed and approved the statistical analysis plan. The current SAP will support trial protocol .

Data will be entered and analysed in Stata 16.

We will aim to follow this SAP unless it is not appropriate to do so and will report deviations from the SAP in the publication.

### 1.2. PURPOSE AND SCOPE OF THE PLAN

The purpose of the plan is to describe the analysis of the primary, secondary, exploratory and mechanistic outcome measures as stated in the protocol. No interim analysis is planned.

### 1.3. TRIAL OVERVIEW

Please see sections 1 (background) and 2 (methods and analysis) of the protocol .

### 1.4. OBJECTIVES AND OUTCOME MEASURES

Table 1 lists the primary and secondary outcome measures, an exploratory outcome measure, and mechanistic outcome measures. Table 1 corresponds to the primary, secondary and mechanistic outcome measures listed in Table 2 of the published protocol . Exploratory and process outcome measures are now listed in separate sections below.

| Table 1 Objectives and outcome measures |                                                              |                      |                             |
|------------------------------------------------|--------------------------------------------------------------|----------------------|-----------------------------|
|                                                | Objectives                                                   | Outcome Measures     | Time point(s)               |
| Primary                                 | Self-reported depression severity at post-treatment (week 6) | PHQ-9                | Weeks 6                     |
| Secondary                               | Self-reported depression severity during follow-ups          | PHQ-9                | Baseline, weeks 2, 4, 6, 12 |
| Secondary                               | Remission of depression                                      | PHQ-9 score $\leq 4$ | Baseline, weeks 6           |
| Secondary                               | Anxiety                                                      | GAD-7                | Baseline, weeks 2, 4, 6, 12 |
| Secondary                               | The inability to experience pleasure (i.e. anhedonia)        | SHAPS                | Baseline, week 6, 12        |
| Secondary                               | Cognitive functioning                                        | PDQ-5                | Baseline, week 6, 12        |
| Secondary                               | Health-related quality of life                               | SF-12                | Baseline, week 6, 12        |
| Secondary                               | Functional outcome                                           | WSAS                 | Baseline, week 6, 12        |

|                    |                                                                  |                                |                      |
|--------------------|------------------------------------------------------------------|--------------------------------|----------------------|
| Mechanistic | Changes in cortisol level for awakening response                 | Saliva sample (home test kits) | Baseline, week 6     |
| Mechanistic | Changes in gut microbiome for all species                        | Stool samples (home test kits) | Baseline, week 6     |
| Mechanistic | Changes in reward sensitivity                                    | PILT                           | Baseline, week 6, 12 |
| Mechanistic | Changes in the inability to experience pleasure (i.e. anhedonia) | SHAPS                          | Baseline, week 6, 12 |

Note: PHQ-9, Patient Health Questionnaire-9; GAD-7, General Anxiety Disorder Scale; SHAPS, Snaith-Hamilton Pleasure Scale; PDQ-5, Perceived deficits questionnaire-5-item; SF-12, SF Short-Form 12 Health Survey; WSAS, Work and Social Adjustment Scale; PILT, Probabilistic instrumental learning task.

## 2. TRIAL DESIGN

Figure 1 shows the CONSORT Flow Diagram of our parallel randomized controlled trial, as described below.

[figure not shown]

**Figure 1 CONSORT Flow Diagram**

## 2.1. TARGET POPULATION

Eligible participants are adults aged 18-65 years with depression, who have been treated with at least two antidepressants in the current episode but still have moderate or severe depression ( $\geq 15$ ) as assessed by PHQ-9.

Detailed inclusion/exclusion criteria are listed in the protocol.

## 2.2. SAMPLE SIZE

We consider a 5-point difference in PHQ-9 total score (0-27 scale) to represent a minimum clinically important difference, as suggested by Lowe et al. This study reported that the SD of the change in PHQ-9 over 3 months as 5.8 and as 6.1 over 6 months. Assuming an SD of 6 over 6 weeks would suggest a standardised effect size of 0.83 in PHQ-9 to be clinically relevant. The sample size to test differences between groups at 90% power and at a type one error rate of 5% would be 64 (32 per group). A sample size of 100 participants will be recruited in case of 35% attrition/missing data. In simulations we confirmed that this sample size remains robust under scenarios such as unequal sizes of the strata used in minimisation. In actuality, recruitment was stopped when 88 people were randomised because it was clear that follow-up rates were substantially higher than predicted, meaning that we were on track to achieve more than 64 people contributing to the primary outcome and achieving sufficient power.

## 2.3. RANDOMISATION AND BLINDING IN THE ANALYSIS STAGE

With minimisation (based on BMI [less than 30 kg/m^2 vs. 30+ kg/m^2] and PHQ-9 [15-19, moderately severe] vs. [20-27, severe]) and 1:1 ratio. Details including the allocation concealment mechanism are described in the 2.6 section of the protocol.

## 3. ANALYSIS – GENERAL CONSIDERATIONS

### 3.1. DESCRIPTIVE STATISTICS

A table will present the baseline characteristics. This table will include depression severity (continuous), duration of current depression (continuous), current antidepressant medication use (categorical), all secondary outcome scores (continuous), age (continuous), sex (categorical), ethnic group (categorical), education (categorical), area of deprivation (categorical), BMI (continuous), smoking status (categorical), alcohol consumption (continuous), illicit drug use (binary), and health conditions (T2DM, hypertension, CVD). Continuous variables will be summarised using means and standard deviations. Medians with interquartile ranges will be presented where appropriate. Categorical variables will be summarised using frequency counts and percentages.

### 3.2. DEFINITION OF POPULATION FOR ANALYSIS

Primary analysis: Given the nature of the study, all randomised participants with at least one measurement on the outcome of interest will be included in the primary intention-to-treat analysis in the group they were randomised.

Safety analysis (serious adverse event): This will include participants who commenced the ketogenic diet compared with all those who commenced the Phyto diet.

The per-protocol population is characterised by:

- health coaches selecting 'Completely/Every Day' or 'Mostly/Most of the Days', when assessing participants' adherence to the diet, in at least 5 out of the (up to) 6 follow-

up calls. (Note on missing data: participants responding to fewer than 5 calls will not be considered adherent)

## 4. PRIMARY ANALYSIS

### 4.1. PRIMARY OUTCOMES

The change in PHQ-9 scores from baseline to week 6 will be compared between groups. Initially, data will be plotted in the following tables. A linear contrast will be used to test the difference between groups in changes from baseline to week 6 in PHQ-9 scores. Two-tailed tests and a significance level of 0.05 will be used.

The statistical analysis of the primary outcome, effectiveness of the intervention for weight loss, will be carried out both on the basis of intention-to-treat (ITT) and per-protocol (PP). For the ITT analysis, participants will be analysed according to their allocated intervention group. For the per-protocol analysis, we will include participants who, in at least 5 out of the 6 follow-up calls, were rated by health coaches as adhering to the diet at levels of "Completely/Every Day" or "Mostly/Most of the Days".

In both cases, a linear mixed effect model that includes treatment group, time (categorical) and their interaction as fixed effects, and individual subjects as random effects will be fit using PHQ-9 at all available assessments. We will include stratification variables (BMI values and PHQ-9) as continuous variables.

The primary and secondary treatment effects will be given by the interaction between timepoint and treatment. We will present the outcome in the original units of the scale and calculate Cohen's d.

Normality of residuals will be checked graphically. If there are substantial violations from normality in the primary analysis then a non-parametric *p*-value will be calculated by permutation testing. For binary outcomes, we will use analogous generalised linear models.

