### 2. Inclusion Criteria

- Aged 18-65 years
- Have been diagnosed with depression
- Have had 2 or more antidepressant treatment trials of adequate dose and duration within the current depressive episode to which they did not fully respond. An adequate treatment trial is defined as at least 4 weeks of a medication at a minimum NICE-approved dose
- With a Patient Health Questionnaire-9 (PHQ-9) total score greater than or equal to 15 at baseline
- Able to understand and be willing to adhere to the demands of the study
- Provision of written informed consent
- Have access to a tablet/computer for online assessments, follow-ups with the registered dietitian, and able to attend appointments for assessments and treatment and adhere to study procedures
- Have both a fridge and a freezer at home
- Complete all baseline assessments

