### 4.2. SECONDARY OUTCOMES

Proportion achieving remission (PHQ9≤4) will be analysed using a mixed effect logistic regression model. If convergence fails, then week 6 and week 12 will be analysed as separate logistic regression models.

Secondary outcome measures will be analysed using analogous models to the primary outcome. This will include linear models adjusting for treatment group, baseline value of the dependent variable, and the stratification factors (BMI and PHQ-9).

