## 5. SECONDARY ANALYSIS

Analysis of the primary analysis population will be repeated with additional adjustments for age, sex and presence of comorbidities (T2DM, hypertension, CVD).

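### As written, the primary mixed model makes its covariate adjustment inert and rests the week-6 standard error on an unstated, probably ill-fitting covariance

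*Combined protocol and SAP*

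**What the plan says.** SAP 4.1 (Primary outcomes) specifies, for both the intention-to-treat and the per-protocol analysis, "a linear mixed effect model that includes treatment group, time (categorical) and their interaction as fixed effects, and individual subjects as random effects". The response is PHQ-9 at every available assessment, which SAP Table 1 lists as baseline and weeks 2, 4, 6 and 12. The tested quantity is the between-arm difference in change from baseline to week 6, taken from the time-by-treatment interaction. The section adds: "We will include stratification variables (BMI values and PHQ-9) as continuous variables". On testing it says: "Two-tailed tests and a significance level of 0.05 will be used". It names no residual covariance, random slope, robust variance or degrees-of-freedom method. Protocol Section J, item 4, gives the same model without covariates.

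Three other places bear on this:

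- SAP 5 (Secondary analysis): "Analysis of the primary analysis population will be repeated with additional adjustments for age, sex and presence of comorbidities (T2DM, hypertension, CVD").
- SAP 4.2 (Secondary outcomes) calls its models analogous to the primary one, yet describes "linear models adjusting for treatment group, baseline value of the dependent variable, and the stratification factors (BMI and PHQ-9").
- Protocol Section F.2 admits only people with a PHQ-9 "total score greater than or equal to 15 at baseline".

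**The concern.** With baseline PHQ-9 among the responses, the week-6 interaction is a within-person contrast. A covariate that is constant over time and enters only as a main effect shifts all five visits of a person equally, so it drops out of that contrast. The estimate labelled as adjusted for PHQ-9 and BMI would in fact be the raw difference in change scores. The SAP 5 analysis would be reported as a robustness check although its agreement with the primary result is close to guaranteed.

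Separately, a random intercept with one residual variance imposes equal variances at all visits and equal correlations between all pairs of visits. Entry confines baseline to 15–27, while follow-up scores can range over 0–27. If the imposed pattern fails, the single confirmatory p-value and its confidence interval are miscalibrated. That matters most for a borderline result.

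**Working it through.** **1. The plan's own figure.** SAP 2.2 states: "We consider a 5-point difference in PHQ-9 total score (0-27 scale) to represent a minimum clinically important difference". It assumes an SD of change of 6, so the standardised effect is 5/6 = 0.83. The sample size "at 90% power and at a type one error rate of 5% would be 64 (32 per group") reproduces: the two-sample t-test needs 31.3, so 32 per arm, with power 90.7%. Allowing for 35% loss, 64/0.65 rounds up to 99, against 100 planned. SAP 2.2 reports 88 randomised; taken as 44 per arm, power is 97.2% with complete data. The standard error implied by the plan is then 6 × sqrt(2/44) = 1.28.

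**2. Do the covariates act?** The model was fitted by REML to simulated data, 44 per arm, five visits.

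- Complete data: in one fit the week-6 interaction was 0.7045 with SE 1.0188 in each of three models (no covariates; PHQ-9 and BMI; PHQ-9, BMI and age). In 80 simulations for each of three covariance settings, the change in estimate and in SE was 0.0000 throughout.
- About 12% of visits missing: the estimate moved 0.02 to 0.08 points on average (largest 0.27) and the SE by at most 0.02.

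The complete-data result is algebraic and does not depend on the assumed covariance.

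**3. Which variance does the model use?** With complete data, the random-intercept SE of any visit contrast is sqrt(V × (1/n1 + 1/n2)), where V is the mean of var(Yj − Yk) over the 10 visit pairs. The correct SE uses var(Y6 − Y0) in place of V. Assume baseline SD s0, a common follow-up SD sf, correlation r0 between baseline and each follow-up, and rf between follow-ups:

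- 4 baseline pairs: A = s0² + sf² − 2·r0·s0·sf
- 6 follow-up pairs: B = 2·sf²·(1 − rf)
- V = (4A + 6B)/10; SE ratio = sqrt(V/A); true level = 2 × [1 − Φ(1.96 × ratio)]

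| s0 / sf | r0 / rf | A | B | V | SE ratio | True level |
|---|---|---|---|---|---|---|
| 6 / 6 | 0.5 / 0.5 | 36.0 | 36.0 | 36.00 | 1.00 | 5.0% |
| 3 / 6 | 0.4 / 0.7 | 30.6 | 21.6 | 25.20 | 0.91 | 7.5% |
| 3 / 6 | 0.3 / 0.7 | 34.2 | 21.6 | 26.64 | 0.88 | 8.4% |
| 3 / 6 | 0.3 / 0.8 | 34.2 | 14.4 | 22.32 | 0.81 | 11.3% |
| 3 / 6 | 0.4 / 0.4 | 30.6 | 43.2 | 38.16 | 1.12 | 2.9% |

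In the third row the model SE is sqrt(26.64 × 2/44) = 1.10 against a correct 1.25.

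**4. Range.** Over 145 assumed patterns with SD of change 5.5–6.5 (s0 2.5–4, sf 5–6.5, r0 0.2–0.6, rf 0.5–0.9), the SE ratio runs from 0.70 to 1.09 and the true level from 3.2% to 17.0%, median 8.5%.

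**5. What the documents themselves constrain.** A unimodal baseline confined to 15–27 has SD at most 4. With SD of change 6 and a non-negative correlation, the week-6 SD is at least sqrt(36 − 16) = 4.5, so unequal variances are expected. The test exceeds its nominal level when B < A, that is, with A = 36, when rf > 1 − 18/sf². At r0 = 0.3 and s0 of 2.5 to 4, that threshold is 0.54 to 0.47.

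**The case against.** The strongest reply is that SAP 4.1 does not say what is criticised. It names no covariance structure, so a random intercept alone is an inference. SAP 4.2 points towards baseline as a covariate, and if baseline were not a response row, the inert-covariate argument would fall. Part of this stands: the wording is silent on covariance, and 4.1 and 4.2 conflict. But subject is the only dependence term given, and a contrast of change from baseline needs baseline among the responses. The ordinary reading therefore holds until the SAP says otherwise.

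A reader might go further and infer that the week-6 standard error is simply wrong. The documents do not support that. They give no baseline SD and no between-visit correlations. The error vanishes under compound symmetry and reverses in some patterns (2.9% in the last row of the table). A compressed baseline alone does not make the test too liberal; follow-up visits must also correlate closely enough with each other. Nor does using baseline twice cause the standard-error problem: that comes from the pooled within-person variance, whereas the double use explains the inert adjustment.

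A reader might also infer a material bias from chance baseline imbalance. That is not supported either. Allocation is minimised on PHQ-9 severity, the change-score contrast is unbiased under randomisation, and preferring baseline adjustment is an argument about precision. The gain can be small: residual SD 5.50 instead of 5.53 with s0 = 3, sf = 6 and r0 = 0.4, though 5.20 instead of 6.00 under compound symmetry with r = 0.5.

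Nothing else in the SAP closes the gap. The permutation p-value in 4.1 is triggered only by non-normal residuals, and the sensitivity analyses in 4.5 and 4.6 name no alternative covariance.

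**Conclusion.** The point stands in two parts, as a should-fix.

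First, on the ordinary reading of SAP 4.1, the PHQ-9 and BMI adjustment and the SAP 5 covariates have no effect on the week-6 result in complete data and almost none with missing visits. It would be too strong to say that every covariate in the plan does nothing: the logistic model for remission and any genuinely baseline-adjusted model under 4.2 are unaffected.

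Second, the standard error is likely miscalibrated, more often too small. The true level is about 3% to 17% under the assumed covariances, and 8.4% at s0 = 3, sf = 6 and correlations 0.3/0.7. Direction and size rest on correlations that the documents do not give. A follow-up correlation above the baseline correlation is plausible but assumed. Sample size and power at a 5-point effect are not in question.

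**What to change.** Rewrite the model in SAP 4.1:

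- State an unstructured, visit-specific residual covariance, REML, a small-sample degrees-of-freedom method such as Kenward-Roger, and one named fallback for non-convergence, such as heterogeneous Toeplitz or a robust variance.
- Use baseline PHQ-9 once. Either (a) take weeks 2, 4, 6 and 12 as responses, with arm-by-week and baseline-by-week terms; or (b) keep baseline as a response with a common mean across arms.
- Enter BMI and the SAP 5 covariates with by-week terms, and define the effect as the arm contrast at week 6.
- Give the continuous secondary outcomes in 4.2 the same form, so that the two sections agree.

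The cost is SAP wording and a few lines of Stata, and perhaps a slightly wider confidence interval. Under (a), participants with only a baseline score leave the model although SAP 3.2 counts them in the intention-to-treat population; (b) keeps them. SAP 1.1 already commits to reporting deviations. If primary results have been seen, as SAP 10 may suggest, report the re-specified model beside the written one and label it as a deviation.
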